### Study measurements and data collection

2.6

Disease severity will be evaluated via mRS and CASE, See Table 1 for the specific schedule of assessments for each visit.

**Table 1 tab1:** Schedule of enrolment, interventions, and assessments.

	Study period																			
	Screen	Treatment phase													Follow-up					
Time point (week)	−1	0	1	2	3	4	5	6	7	8	12	16	20	24	28	32	36	40	44	48
Enrolment																				
Informed consent	**×**																			
Demographics	**×**																			
Medical history	**×**																			
Inclusion/exclusion	**×**																			
Intervention																				
Ofatumumab		**×**	**×**	**×**		**×**				**×**	**×**	**×**	**×**	**×**	Depends on the level of memory B cells monitored					
Daratumumab		**×**	**×**	**×**		**×**				**×**	**×**	**×**	**×**	**×**						
Rituximab		**×**												**×**	Depends on the level of memory B cells monitored					
IVIG/PE						**×**				**×**	**×**									
Assessments	×																			
HCG test (for female participants)	**×**																			
Physical examination	**×**	**×**	**×**	**×**	**×**	**×**	**×**	**×**	**×**	**×**	**×**	**×**	**×**	**×**	**×**	**×**	**×**	**×**	**×**	
Clinical blood tests and biochemistry	**×**		**×**	**×**		**×**				**×**	**×**	**×**	**×**	**×**			**×**			**×**
Cerebrospinal fluid (CSF) Analysis	**×**																			
Serum immunoglobulin and anti-NMDAR antibody levels	**×**					**×**				**×**	**×**	**×**	**×**	**×**			**×**			**×**
CSF anti-NMDAR antibody levels)	**×**																			
Lymphocyte Subsets	**×**		**×**	**×**		**×**				**×**	**×**	**×**	**×**	**×**			**×**			**×**
Memory B cells and plasma cell subsets	**×**		**×**	**×**		**×**				**×**	**×**	**×**	**×**	**×**			**×**			**×**
mRS	**×**	**×**	**×**	**×**	**×**	**×**	**×**	**×**	**×**	**×**	**×**	**×**	**×**	**×**	**×**	**×**	**×**	**×**	**×**	**×**
CASE	**×**	**×**	**×**	**×**	**×**	**×**	**×**	**×**	**×**	**×**	**×**	**×**	**×**	**×**	**×**	**×**	**×**	**×**	**×**	**×**
MMSE	**×**	**×**	**×**	**×**	**×**	**×**	**×**	**×**	**×**	**×**	**×**	**×**	**×**	**×**	**×**	**×**	**×**	**×**	**×**	**×**
MOCA	**×**	**×**	**×**	**×**	**×**	**×**	**×**	**×**	**×**	**×**	**×**	**×**	**×**	**×**	**×**	**×**	**×**	**×**	**×**	**×**
NPI	**×**	**×**	**×**	**×**	**×**	**×**	**×**	**×**	**×**	**×**	**×**	**×**	**×**	**×**	**×**	**×**	**×**	**×**	**×**	**×**
Imaging	**×**													**×**						**×**

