#### Definition of the primary efficacy endpoint and event definitions

2.12.1

The primary efficacy endpoint is the proportion of patients with an mRS score ≤ 2, assessed at 16 weeks after treatment initiation.

Relapse event: Defined as the occurrence of new or worsening neurological or psychiatric symptoms attributable to NMDARE following an initial period of at least 2 months of clinical improvement or stabilization, accompanied by at least one of the following: (1) recurrence or an increase in anti-NMDAR antibodies in cerebrospinal fluid (CSF) or serum; (2) new or worsening abnormalities on brain MRI consistent with encephalitis; or (3) new or increased epileptiform activity on EEG. All relapse events must be reviewed and confirmed by an independent adjudication committee (6, 21, 27, 28).

Rescue treatment event: Defined as the initiation of any additional immunotherapy beyond the assigned study treatment due to insufficient clinical improvement, clinical deterioration, or life-threatening complications. This includes, but is not limited to, cyclophosphamide, bortezomib, tocilizumab. The decision to initiate salvage therapy is made by the treating physician and subsequently reviewed and confirmed by the independent adjudication committee (21, 29).

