#### Analysis methods for primary and secondary endpoints

2.12.2

For the primary endpoint, the comparison of the proportion of patients achieving mRS ≤ 2 at week 16 between treatment groups will be performed using a Cochran–Mantel–Haenszel test stratified by study center, with a two-sided significance level of 0.05. A logistic regression model adjusting for stratification factors and baseline covariates (e.g., age, baseline mRS) will be used as a supportive analysis.

For time-to-event endpoints, including relapse and salvage treatment events, Kaplan–Meier curves will be used to summarize event times, and event rates with 25%/75% quartiles will be calculated. The stratified log-rank test will be used for intergroup comparisons, and hazard ratios with 95% confidence intervals will be estimated using a Cox proportional hazards model, with stratification factors included as covariates.

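### One of the three findings that can confirm a relapse is an antibody that the daratumumab sequence is meant to lower, so the relapse comparison between arms may partly reflect the definition

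*Protocol article*

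**What the plan says.** Section 2.12.1 of the protocol article defines a relapse in three layers.

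- A clinical layer: neurological or psychiatric symptoms of NMDARE that appear or get worse "following an initial period of at least 2 months of clinical improvement or stabilization".
- A supporting layer, which is mandatory. The symptoms must be "accompanied by at least one of the following: (1) recurrence or an increase in anti-NMDAR antibodies in cerebrospinal fluid (CSF) or serum". The second alternative is an imaging finding, given as "2) new or worsening abnormalities on brain MRI consistent with encephalitis". The last alternative is electrophysiological and reads "or (3) new or increased epileptiform activity on EEG".
- A confirmation layer: "All relapse events must be reviewed and confirmed by an independent adjudication committee".

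Section 2.12.2 makes relapse a time-to-event outcome: "For time-to-event endpoints, including relapse and salvage treatment events, Kaplan–Meier curves will be used to summarize event times". The arms are compared by a stratified log-rank test, and hazard ratios come from a Cox model.

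Four other places bear on this. Section 2.10 lists the change in serum autoantibody from baseline to week 16 as a secondary endpoint; relapse is not on that list. The Introduction gives the reason for adding daratumumab: it eliminates antibody-secreting plasma cells that anti-CD20 treatment spares. Section 3 names lower titres of the pathogenic antibody among the effects under study. Section 2.1 states that the trial is open-label.

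**The concern.** A clinical event should be counted by the same rule in every arm, and that rule should not draw on a laboratory marker that one arm's treatment is designed to move. Here a patient with clear clinical relapse is not an event unless an antibody, MRI or EEG finding supports it. If daratumumab suppresses antibody production as intended, it may also blunt the rise that would have confirmed the relapse.

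At stake is the reading of the relapse hazard ratio. A value below 1 for the daratumumab arm would naturally be read as fewer clinical relapses. Part of it could instead mean that clinical relapses in that arm were confirmed less often. The open-label design adds to this, because those who refer a suspected relapse know the arm.

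**Working it through.** The document gives no relapse rate and no frequency for any of the three supporting findings, so no size can be computed. The check is to set the passages side by side and follow the definition through to the estimate.

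1. **Is support mandatory?** Yes. Section 2.12.1 requires at least one of the three findings in addition to symptoms, so a purely clinical relapse is not an event.

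2. **Is one finding an intended treatment effect?** Yes. The Introduction and Section 3 describe plasma cell depletion and titre reduction as the purpose of the sequence. Section 2.10 measures antibody change as an outcome. The same marker is thus both a response measure and a route to confirming a clinical event. Ofatumumab is given in both active arms, so daratumumab is what separates them.

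3. **Does it reach a comparison between arms?** Yes, through the log-rank test and Cox model of Section 2.12.2.

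4. **What does the comparison then estimate?** Let h be an arm's hazard of clinical relapse and c the probability that such a relapse has at least one supporting finding. The hazard of counted relapse is about c × h. With D for the daratumumab arm and O for ofatumumab alone:

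   counted ratio ≈ (h_D / h_O) × (c_D / c_O)

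   The counted ratio equals the clinical ratio only if c_D = c_O. Because c = 1 − P(none of the three findings), the antibody criterion enters c. It matters only for relapses that MRI and EEG do not already support.

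5. **Which way would c_D / c_O move?** If daratumumab suppresses antibody production, fewer relapses would show a rise, and the factor would lie below 1. But the criterion compares a patient with that patient's own earlier result. A patient driven to a low or negative titre may show a recurrence more readily, which pushes the factor upwards. The first effect is the more natural expectation given the trial's rationale, but nothing in the document settles it.

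6. **Does blinding close the gap?** Not as written. Section 2.6 describes blinded video review for outcome evaluations and names mRS, CASE and the neurocognitive assessments. Section 3 says in general terms that outcome assessors are blinded, without naming relapse. Section 2.12.1 calls the relapse committee independent and says nothing on blinding. Even a committee blinded to arm would still apply a criterion whose result carries the treatment effect, so blinding to arm alone is not enough.

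7. **Does it touch the primary analysis?** No. The primary endpoint is mRS ≤ 2 at week 16, and the sample size in Section 2.11 rests on it alone.

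**The case against.** The case for leaving the definition alone is substantial. Requiring objective support is a legitimate choice in favour of specificity, made with cited references and followed by committee review. Antibody is one of three alternatives, and a relapse supported by MRI or EEG is counted whatever the titre. Antibody lowering by daratumumab is the trial's hypothesis, not a result, and the within-patient form of the criterion leaves the direction open. Relapse is not a listed secondary endpoint, and a sensitivity analysis could well sit in an analysis plan that is not shown. All of this stands, and it limits the point to a minor one. It does not remove the dependence itself: if the trial's hypothesis is right, the published definition may favour the daratumumab arm.

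Three stronger readings are tempting, and the document does not support them.

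- **Confirmation depends on calendar time.** In Table 1 the row "Serum immunoglobulin and anti-NMDAR antibody levels" is 4-weekly from week 4 to week 24, then only at weeks 36 and 48, and imaging after screening is at weeks 24 and 48. A reader might infer that late relapses are harder to confirm. But relapse is triggered by symptoms. Testing prompted by a suspected relapse is neither described nor excluded, and a condensed article may leave it out. The schedule is also the same in all arms: a c that changes over time but equally in each arm cancels from the ratio in step 4. It could cost events, but it does not by itself bias the hazard ratio.
- **The EEG criterion has no comparator.** Table 1 has no EEG row. Nothing in the document rules out a comparison with an EEG done at diagnosis or in routine care.
- **The distortion can be given a number.** Any figure would need support probabilities by arm, which the document does not give. Choosing them in one direction only would restate the premise.

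**Conclusion.** The point holds as a minor one. The relapse definition lets a marker that the daratumumab sequence is intended to lower decide whether some clinical relapses are counted, and relapse is then compared between arms in an open-label trial whose relapse committee is not described as blinded. A lower relapse hazard with daratumumab could partly reflect the definition.

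This rests on two assumptions: that daratumumab reduces antibody rises as intended, and that some relapses would have antibody as their only supporting finding. Neither can be checked from the document.

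**What to change.** Make two changes.

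1. Have sites send every suspected clinical relapse to the adjudication committee, including those without a supporting finding. The committee first judges whether a clinical relapse occurred, blinded to arm and to antibody result. The antibody, MRI and EEG findings are then added to classify the same case under the planned definition. State in Section 2.12.1 that the committee is blinded.

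2. Add to Section 2.12.3 a sensitivity analysis of symptom-based relapse as judged in that first step, without the antibody criterion and dated at symptom onset, and report it beside the planned analysis. If the two hazard ratios agree, the definition is not driving the result. If they differ, the reader can see by how much.

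The cost is one further analysis, a committee charter entry, and review of the suspected cases that lack a supporting finding. The downside is that clinical-only relapse is less specific, since other causes of worsening may be included. That is why it should accompany the planned definition and not replace it. No treatment, visit or sample size changes.

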#### Analysis methods for primary and secondary endpoints

2.12.2

For the primary endpoint, the comparison of the proportion of patients achieving mRS ≤ 2 at week 16 between treatment groups will be performed using a Cochran–Mantel–Haenszel test stratified by study center, with a two-sided significance level of 0.05. A logistic regression model adjusting for stratification factors and baseline covariates (e.g., age, baseline mRS) will be used as a supportive analysis.

For time-to-event endpoints, including relapse and salvage treatment events, Kaplan–Meier curves will be used to summarize event times, and event rates with 25%/75% quartiles will be calculated. The stratified log-rank test will be used for intergroup comparisons, and hazard ratios with 95% confidence intervals will be estimated using a Cox proportional hazards model, with stratification factors included as covariates.

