**Study design:**

This multicenter, open-label, randomized controlled trial is conducted across 58 tertiary hospitals in China. Eligible participants are patients with severe AE especially NMDARE (mRS ≥ 3 points and neuropsychiatric manifestations inadequate to symptomatic treatment) post first-line immunotherapy. A total of 200 patients will be randomized at a 2:2:1 ratio into three groups. 80 patients will receive B-cell depleting agent (anti-CD20 mAb ofatumumab) followed by anti-CD38 mAb daratumumab, 80 patients will receive B-cell depleting agent ofatumumab alone, and 40 receive repeated IVIG or plasmapheresis.

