### Trial design and setting

2.1

RADIA is a randomized, controlled, open-label, multicenter clinical trial initiated by investigators to assess the safety and efficacy of B-cell depleting therapy followed by daratumumab in patients with severe AE, with NMDARE as the primary target population. The study will be conducted in the Department of Neurology in 58 tertiary hospitals nationwide, with a planned enrollment of 200 patients by December 2026.

The study was approved firstly by the Institutional Review Board of the Third Affiliated Hospital of Soochow University. The first patient was randomized in Jan 2025. The participants will be randomly assigned to receive one of three treatment arms: B-cell-depleting agents (ofatumumab followed by daratumumab, B-cell-depleting agents (ofatumumab alone), or repeated IVIG/PE therapy. The flowchart outlining the recruitment, intervention, and evaluation processes is presented in Figure 1.

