### Randomization and treatment allocation

2.3

Randomization is performed using a dedicated and password-protected clinical trial platform, Data Acquisition Platform–Electronic Data Capture system (DAP-EDC). Eligible patients are assigned in a 2:2:1 ratio to the three treatment groups. Stratified block randomization was applied, with study center as the stratum. Subjects were allocated sequentially according to their enrollment time.

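### The primary CMH test is stratified by 58 centres sharing 200 patients, a loss of information that the unstratified sample size did not allow for

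*Protocol article*

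**What the plan says.** Section 2.12.2 names the primary test. The comparison of the proportions with mRS ≤ 2 at week 16 "will be performed using a Cochran–Mantel–Haenszel test stratified by study center, with a two-sided significance level of 0.05". The supportive analysis is described as follows: "A logistic regression model adjusting for stratification factors and baseline covariates (e.g., age, baseline mRS) will be used as a supportive analysis". For relapse and rescue treatment, a stratified log-rank test is planned, and "hazard ratios with 95% confidence intervals will be estimated using a Cox proportional hazards model, with stratification factors included as covariates".

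Section 2.3 makes centre the only stratification factor: "Stratified block randomization was applied, with study center as the stratum". Section 2.1 gives the scale: "58 tertiary hospitals nationwide, with a planned enrollment of 200 patients by December 2026". Allocation is 2:2:1.

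Section 2.11 sizes the two active arms from 90% v 70%, two-sided α of 0.05 and 80% power. It reaches 64 per group, then 80 per group after a 10% dropout allowance. It does not mention stratification.

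**The concern.** A centre contributes to a centre-stratified CMH statistic only if it holds patients from both arms and both outcomes among them. With two or three patients per centre in the powered comparison, many centres fail that condition, and others contribute with unbalanced arms. The sample size in section 2.11 assumes that every patient counts in full, so the test named and the calculation that supports it do not match.

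What is at stake is power for the main question in a rare disease, where extra patients are hard to find. There is a second, conditional issue. Centre is the only stratification factor, so adjusting the logistic and Cox models for stratification factors means adjusting for centre. If that is done with one fixed term per centre, the logistic estimate suffers sparse-stratum bias and would exaggerate the effect it is meant to support.

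**Working it through.** **Inputs from the article.** 58 centres; 200 patients at 2:2:1 (80, 80, 40); response 0.90 v 0.70 (odds ratio 9 / 2.333 = 3.86); two-sided α 0.05; 10% dropout. Average per centre: 200/58 = 3.4 over all arms and 160/58 = 2.8 in the powered comparison.

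**Assumed, because not stated.** Centre sizes (equal, or skewed with gamma weights) and block size (5, the smallest that 2:2:1 permits, or 10).

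**1. The plan's own figure.** With the pooled-variance formula,

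n = [1.96·√(2·0.8·0.2) + 0.842·√(0.9·0.1 + 0.7·0.3)]² / 0.2² = (1.109 + 0.461)² / 0.04 ≈ 62 per group.

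The variant using the average variance throughout gives 63. Both are close to the stated 64, and both are unstratified. Under the same formula, power is 81.5% at 64 per group and 85.9% at 72.

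**2. The margin.** 64/0.9 = 71.1, so 72 per group would cover 10% dropout. The plan recruits 80, which leaves 80 × 0.9 = 72 evaluable, or 8 per arm more than the 64 said to be required.

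**3. Information kept by the stratified test.** The share is Σ(n₁ₖn₀ₖ/nₖ) ÷ (n₁n₀/n), summed over centres k. Trials were simulated with 2:2:1 permuted blocks within 58 centres and 10% dropout (3,000 to 8,000 trials in the main settings; CMH without continuity correction).

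| Block | Centre sizes | Information kept | CMH power, 72 per arm |
|---|---|---|---|
| 5 | equal | 80% | 78% |
| 5 | skewed | about 85% | 80–82% |
| 10 | equal | 69% | 72% |
| 10 | skewed | 80% | 79% |

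The unstratified test has 86–88% in the same settings. With 10 to 20 strata in place of 58, power is about 85–87%; 20 strata keep about 96% of the information.

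**4. Cross-check by formula.** Put the effective size m = 72 × share kept into power = Φ[(0.2√m − 1.109)/0.548].
- 80% kept: m = 57.6, power 77%.
- 85% kept: m = 61.2, power 80%.
- 69% kept: m = 49.7, power 71%.

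These agree with the simulated values to within about two points.

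**5. At the stated 64 per group.** Simulated centre-CMH power is about 62–75% across the settings, against 81–83% unstratified. The 80% claimed for 64 per group is therefore not what the named test delivers.

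**6. Type I error of the CMH.** With equal centres, no dropout and 70% response in both arms, it is 0.049 (8,000 trials). Other settings gave 0.037 to 0.063. It is nominal.

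**7. Supportive logistic model, only if centre is fitted as fixed terms by unconditional maximum likelihood.** The true odds ratio is 3.86. The median estimate is 8.1 with equal centres, 9.0 with equal centres and 10% dropout, and 5.1–5.8 with skewed centres. Wald type I error is 0.105–0.125 with equal centres and 0.064–0.089 with skewed centres, at nominal 0.05.

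**The case against.** The strongest reply is that the primary test is valid. CMH tolerates many small strata, and stratifying the analysis by the randomisation factor is standard practice. At the planned 10% dropout and with blocks of 5, power is 78–82%, which is roughly what was promised. All of this stands. A reader might infer that the primary result would be invalid or that power collapses; neither follows. The issue is efficiency. The reply does not remove it, because power stays near 80% only through the step from 72 to 80 patients per arm, which the article presents as dropout cover, and because blocks of 10 with even recruitment bring it down to 72%.

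A second reply is that pooling rules and the handling of centre in models belong in a statistical analysis plan that is not shown. That holds for the logistic model. A reader might infer that its odds ratio is inflated and its type I error doubled. Section 2.12.2 does not say that centre enters as fixed terms fitted by unconditional likelihood; a random intercept or a conditional likelihood fits the same wording and avoids the bias. Even under the fixed-term reading, error near twice nominal needs even recruitment, and the model is labelled supportive. The reply does not hold for the primary test, where the article affirmatively names centre as the stratum.

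Third, any single figure for the loss depends on centre sizes and block size that the article does not give. This is right, and it is why ranges are shown.

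**Conclusion.** The point holds as a mismatch between the named primary test and the sample size behind it. At planned dropout the centre-stratified CMH loses roughly 15–31% of the information. Power is about 72–82%, where an unstratified test has 86–88% and a test with 10–20 strata about 85–87%. The ranges rest on all 58 centres sharing the recruitment, equal or gamma-skewed centre sizes, blocks of 5 or 10, and the plan's own 90% v 70%. If far fewer centres recruit, the loss shrinks: 20 active centres would lose about 4%.

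The logistic concern is conditional on fixed centre terms fitted by unconditional maximum likelihood: median odds ratio about 5–9 against 3.86, and Wald type I error about 6–12%. The size of any loss in the log-rank and Cox analyses is not estimated here, because the article gives no relapse or rescue rates. Severity is moderate.

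**What to change.** Before the analysis is locked:

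- Replace the 58 centre strata in the primary CMH with a small number of pooled strata fixed in advance, for example about 10 regions.
- Use the same pooled strata in the stratified log-rank test and the Cox model.
- In the supportive logistic model, state how centre is handled: pooled strata, a random centre intercept or conditional logistic regression, but not up to 57 fixed terms by unconditional likelihood.
- Restate the power for the test actually used, with the assumed centre sizes and block size.

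Adding baseline mRS to the primary analysis is optional. It is already collected and is named as a covariate in the supportive model, but any gain depends on a prognostic strength that the article does not give.

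The cost is wording and one recalculation; randomisation, treatment and data collection are unchanged. The small downside is that the analysis no longer conditions on every centre, so it may be slightly conservative if centre effects are large.

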Concomitant medications and dosage	**×**	**×**	**×**	**×**	**×**	**×**	**×**	**×**	**×**	**×**	**×**	**×**	**×**	**×**	**×**	**×**	**×**	**×**	**×**	**×**
Statistical analysis												**×**								**×**

Assessments will be conducted by the study team before randomization; after each study drug cycle at weeks 6, 16, and 24; and during follow-up at week 48. Neurocognitive performance will be measured via the Mini-Mental State Examination (MMSE), the Montreal Cognitive Assessment (MoCA), and the Neuropsychiatric Inventory (NPI) will be anti-neuronal antibody titres and other relevant markers will be analysed in serum and cerebrospinal fluid at baseline and week 16 following the initiation of the study drug treatment. For further details, please refer to the enrollment, intervention, and assessment schedule outlined in Table 1. Routine blood parameters will be assessed before each administration of the study drug, on day28 after each cycle, and at week 16 to monitor for potential drug-induced side effects, including thrombocytopenia, leukopenia, and elevated liver enzymes. Additionally, the length of stay in the ICU after the commencement of the study drug will be recorded at the conclusion of the study. Adverse events, including serious adverse events (SAEs), will be monitored continuously from the first administration of the study drug until 1 year after treatment initiation or until withdrawal from the clinical trial, whichever occurs first. Safety monitoring will therefore cover both the treatment period (up to Week 24) and the subsequent follow-up period (Weeks 24–48).

To reduce assessment bias, all outcome evaluations, including mRS, CASE, and neurocognitive assessments are performed by trained neurologists who are not involved in treatment allocation. All assessment sessions are video recorded and subsequently reviewed by at least one additional independent neurologist blinded to treatment group assignment. In cases of discrepancy, a third independent neurologist adjudicates the final score, ensuring that final outcome scores are based on a blinded adjudication process.

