### Outcome measures

2.10

The primary objective of the RADIA study was to determine whether treatment with BCDT followed by daratumumab would yield a more effective and rapid treatment response than standard immunotherapy, as measured by changes in mRS. The mRS is a well-established tool for assessing the degree of dependence and disability in daily activities (26); a decrease in the mRS score indicates increased independence and autonomy. Only patients with an mRS score ≥ 3 were included in the RADIA study, as this score indicates severe disability, where the patient is unable to walk independently and requires assistance with activities of daily living. The primary endpoint of the study was the proportion of patients who achieved an mRS score of ≤ 2 at 16 weeks following treatment initiation.

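### The valid primary week-16 test leaves out baseline mRS, which every patient has; adjusting for it is a near-free improvement worth about −1 to +6 points of power

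*Protocol article*

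**What the plan says.** The endpoint is fixed in section 2.12.1: "The primary efficacy endpoint is the proportion of patients with an mRS score ≤ 2, assessed at 16 weeks after treatment initiation". Section 2.12.2 names the primary test: the comparison "will be performed using a Cochran–Mantel–Haenszel test stratified by study center, with a two-sided significance level of 0.05". The same paragraph adds a logistic model with the stratification factors, in which "baseline covariates (e.g., age, baseline mRS) will be used as a supportive analysis".

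Entry severity is known for everyone. Section 2.10 states: "Only patients with an mRS score ≥ 3 were included in the RADIA study". Section 2.6 says "Assessments will be conducted by the study team before randomization", and Table 1 marks mRS at screening and at week 0. The design does not balance it, since section 2.3 reads: "Stratified block randomization was applied, with study center as the stratum". Section 2.1 has the study "conducted in the Department of Neurology in 58 tertiary hospitals nationwide".

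**The concern.** A patient who enters at mRS 3 reaches the endpoint with a one-point gain; a patient who enters at 5 needs three. Entry mRS is therefore likely to predict response, and the plan itself names it as a covariate. Yet the test that decides the trial does not use it.

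Two things are at stake, both modest. First, some power for ofatumumab plus daratumumab v ofatumumab alone, the contrast that section 2.11 powers. Second, if the arms differ by chance in entry severity, the primary test and the supportive model may point in different directions, and the one that counts is the one that ignores severity.

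**Working it through.** **Inputs from section 2.11.** 90% v 70%, two-sided alpha 0.05, 80% power, 64 per group, 10% dropout, 80 per active arm. Evaluable per arm: 80 × 0.9 = 72.

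**Assumptions, not in the documents.** Entry mRS 3/4/5 in 30/40/30% of patients; odds ratio (OR) of response per mRS point from 1 to 5; 58 centres equally likely to recruit.

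**The plan's own figure.** Pooled two-proportion formula: n = [1.96 × √(2 × 0.8 × 0.2) + 0.8416 × √(0.9 × 0.1 + 0.7 × 0.3)]² / 0.2² = (1.109 + 0.461)² / 0.04 ≈ 62 per group. The stated 64 is reproduced to within two patients. Power by the same formula is 81.5% at 64, 85.9% at 72 and 89.3% at 80 per arm. These figures ignore both centre and baseline mRS.

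**Adding baseline mRS with centre kept.** 4,000 simulated trials per setting, 2:2:1 permuted blocks of five within centre, overall rates held at 90% and 70%. The adjusted analysis is a linear probability model with centre effects and mRS indicators; without mRS, that model matches the planned CMH to within 0.5 points. At 72 per arm:

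| OR per mRS point | Response at entry mRS 3/4/5, ofatumumab alone | Planned CMH by centre | Centre + baseline mRS | Change |
|---|---|---|---|---|
| 1 | 70/70/70% | 79.0% | 77.9% | −1.1 |
| 1.5 | 78/70/61% | 77.6% | 77.3% | −0.3 |
| 2 | 83/71/55% | 77.8% | 79.2% | +1.4 |
| 3 | 89/73/47% | 80.0% | 83.1% | +3.1 |
| 5 | 94/76/38% | 79.0% | 85.0% | +6.0 |

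A repeat simulation gave −1 to 0 at OR 1 to 1.5, +1 at 2, +2 to +3 at 3 and +5 at 5. With 80% response in both arms and OR 3, rejection rates were 4.2% (planned CMH) and 4.7% (centre plus mRS).

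**Separating the centre effect.** A CMH stratified by baseline mRS alone has 87.1%, 85.9%, 87.4%, 90.0% and 91.8% power at OR 1, 1.5, 2, 3 and 5. Most of the distance from the planned test is not due to mRS: at OR 1, where mRS carries no information, power is still 87.1 − 79.0 = 8.1 points higher. That part comes from dropping sparse centre strata. It assumes 58 equal centres and nearly disappears with 20 active ones.

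**Crossing mRS with centre.** With entry mRS at 50/30/20%, using every centre-by-mRS cell as a CMH stratum cut power at 72 per arm to about 47–51% at OR 1.5 to 5, because most cells hold too few patients to inform the comparison.

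**Chance imbalance.** If 30% enter at mRS 5, the between-arm difference in that share has SD √(2 × 0.3 × 0.7 / 72) = 7.6 points. At OR 3 on ofatumumab alone, patients entering at 3 or 4 respond at (0.3 × 89 + 0.4 × 73) / 0.7 = 79.9%, against 47% at entry mRS 5. At those rates, a one-SD imbalance moves the observed difference by 0.076 × (79.9 − 47) ≈ 2.5 points.

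**The case against.** The strongest reply is that nothing here is an error. A CMH test stratified by the randomisation factor, with a covariate-adjusted model in support, is conventional and valid, and baseline mRS is prespecified. Chance imbalance is already allowed for in the type I error. A condensed article need not give the reason for its choice. All of that stands, and it makes this a point of efficiency. It does not remove the gain when baseline mRS is clearly prognostic.

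The second reply is that prognostic strength is unknown and that a weak effect yields nothing. This also stands: at OR 1.5 or below the change is zero or slightly negative.

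A reader might infer more than the documents support:

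- **That power would rise from 86% to 94%.** This follows from multiplying the variance by 1 − 0.5², but it ignores centre and assumes a correlation of 0.5 that the documents do not give. Even at OR 5, with the rates in the table, the covariance of response with entry mRS (scored 0, 1, 2; mean 1, SD √0.6 = 0.775) on ofatumumab alone is (0.4 × 0.76 + 2 × 0.3 × 0.38) − 0.70 = −0.168. The correlation is then 0.168 / (0.775 × 0.458) ≈ 0.47. In the 90% arm (99/94/76%) it is 0.069 / (0.775 × 0.3) ≈ 0.30.
- **That the primary result is unadjusted.** It is stratified by centre.
- **That the whole gap between the planned CMH and an mRS-stratified CMH is due to mRS.** Most of it comes from the centre strata.

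**Conclusion.** The point holds as a near-free improvement, not as a flaw in validity. The primary test omits a baseline value of the endpoint scale that every patient has, so it gives up some efficiency and does not account for chance imbalance in entry severity. At 72 evaluable per arm with centre retained, including it changes power by about −1 to 0 points at OR 1 to 1.5, +1 at 2, +2 to +3 at 3 and +5 to +6 at 5, with type I error near 5%. The size rests on the assumed entry distribution, the assumed prognostic strength and 58 equal centres. On those assumptions the planned CMH has about 78–80% power, so a gain at the upper end could decide whether the 80% target is met.

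**What to change.** By documented amendment before database lock, make the primary analysis of ofatumumab plus daratumumab v ofatumumab alone adjust for baseline mRS (3, 4, 5), defined as the last value before randomisation. Two workable forms:

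- A standardised risk difference from a logistic model with treatment and baseline mRS, with centre pooled or otherwise handled. This stays on the scale of the sample-size assumption. Any removal of centre, the only randomisation stratum, should be justified separately, because its effect on power is a different matter.
- Conditional logistic regression by centre with baseline mRS as covariate, which extends the planned CMH directly. Its power was not simulated; the centre-plus-mRS model above is the nearest analogue.

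Do not cross baseline mRS with the 58 centres as CMH strata. Keep the centre-stratified CMH as the supportive analysis.

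No extra patients or data are needed. The statistical cost is about 1 point of power if baseline mRS is not prognostic. Because the trial is open-label and has been randomising since January 2025, the amendment should be dated and made without sight of outcomes by arm.
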